# Study protocol for a randomized trial comparing two electroacupuncture waveforms for different severity groups of Bell palsy

**DOI:** 10.3389/fneur.2024.1471605

**Published:** 2024-11-20

**Keywords:** Bell palsy, electroacupuncture, waveform, randomized, pilot trial, protocol

## Abstract

**Background:**

Bell palsy (BP) is the most common cause of acute peripheral facial palsy which leads to functional and esthetic disturbances in patients and has a negative influence on daily living. Electroacupuncture (EA) has been considered an alternative treatment for improving facial function in patients with BP. However, there is no agreement on the preferred waveform type of the EA for treating BP.

**Methods:**

This is a study protocol for a pilot randomized, two-arm, three-center, clinical trial at the Third Affiliated hospital of Zhejiang Chinese Medical University, the First Affiliated hospital of Zhejiang Chinese Medical University, and the Hangzhou First People’s Hospital. The trial began in November 2023 and is expected to end in December 2025. Sixty patients with BP whose electroneurography (ENoG) value is at least 20% and 60 patients with BP whose ENoG value is less than 20% will be randomly assigned to the low frequency continuous waveform group or the intermittent waveform group in a 1:1 ratio. Participants will receive 4 weeks of EA treatment and clinical assessments. The primary outcome is the change from baseline score of the Facial Nerve Grading System 2.0. The secondary outcomes include the change from baseline score of the Sunnybrook grading scale and the change from baseline amplitude of the compound muscle action potential of the affected side in the ENoG tests.

**Discussion:**

This is the first study protocol to compare the treatment effect and safety of EA with low frequency continuous waveform and intermittent waveform for different severity groups of BP. This study will contribute to subsequent studies for exploring optimal EA parameters for BP treatment.

**Clinical trial registration:**

ClinicalTrials.gov, NCT06063954.

## Introduction

1

Bell palsy (BP), also known as idiopathic facial paralysis, is a neurological condition that affects facial nerve function with unclear pathogenesis (1). BP is the most common cause of acute facial palsy, accounting for approximately 75% of all cases (2, 3). The reported annual incidence of BP ranges from 11.5 to 53.3 per 100,000 persons in different populations (4, 5). Functional and esthetic impairments are common among individuals with BP, as the most prominent symptom of the condition is the sudden weakness of facial muscles, which usually reaches peak severity within 72 h, leading to a drooping eyelid and corner of the mouth and even the complete loss of facial movement (6). And other symptoms may include decreased taste, hyperacusis, and pain around the ear or jaw (7, 8). In addition, patients with BP may face a heightened risk of psychological disorders, including anxiety and depression, and may also experience a decrease in overall quality of life (9).

Bell palsy has a generally fair prognosis, with most patients experiencing important improvement within 3 weeks (10). Even without intervention, approximately 70% of patients achieve complete recovery within 6 months (2). However, permanent paresis or paralysis occurs in a minority of the patients. The use of electroneurography (ENoG) to objectively measure the severity of facial nerve damage can aid in predicting prognosis (11–13). In ENoG testing, surface electrodes record the compound muscle action potential (CMAP) of facial muscles following electrical stimulation to the main trunk of the facial nerve. The ENoG value is calculated as the ratio of the CMAP amplitude on the impaired side to that on the normal side (14). A previous study showed that an ENoG value of less than 20% predicted a recovery period of at least 4 months, with the possibility of incomplete recovery in the worst cases (15).

Among multiple treatment options for BP, corticosteroids are typically used in the acute phase because of their potent anti-inflammatory effect, with strong evidence demonstrating the benefit for adult patients (16). However, effective treatments for BP in the non-acute stage remain unclear (17). In China, acupuncture has been used in a variety of neurological conditions, including BP. According to a rigorous randomized control trial, manipulating needles to strengthen stimulation during acupuncture provided a stronger therapeutic effect than acupuncture without manipulation in treating BP (18). Electroacupuncture (EA), a treatment that combines traditional acupuncture and electrical stimulation, offers the benefit and convenience of enhancing stimulation through consistent delivery of electrical pulses through the needles. A systematic review showed that EA is more effective than manual acupuncture for BP (19). In clinical practice, controversy exists over whether EA is appropriate for use during the acute stage of BP. Although limited evidence has shown that EA initiation from the acute stage of BP may shorten the recovery time, there are concerns that excessive physical stimulation during the period of nerve degeneration may worsen nerve damage (20, 21). In contrast, the safety of EA when used in the non-acute phase is widely recognized, and a large number of studies have reported its positive effects at this stage (22–24). Notably, as a crucial parameter in EA treatment, the electrical stimulation waveform varies across studies with no consensus on the most effective option. These waveforms mainly include the low frequency or high frequency continuous wave (25), which delivers electrical pulses consistently with a certain frequency, the sparse-dense wave (26), which generates alternating low frequency and high frequency electrical stimulation, and the intermittent wave (23), which delivers electrical pulses in a repeated on–off manner. The lack of a standardized protocol for EA when treating BP poses an obstacle to practitioners.

Previous studies have shown that EA with different waveforms have varying treatment effects. The low frequency continuous waveform at 2 Hz was found to be more beneficial for nerve regeneration than the high frequency continuous waveform at 100 Hz and the sparse-dense waveform at 2/100 Hz (27–29). EA stimulation with the intermittent waveform was found to increase muscle size and enhance muscle excitability (30, 31), and 30–50 Hz are a common frequency range for intermittent waveform (32). While both the low frequency continuous waveform and the intermittent waveform of EA have been proven to have positive effects on neuromuscular function, it is yet to be determined which waveform is more beneficial for the treatment of BP. In addition, the prognosis of BP is significantly impacted by the level of facial nerve damage, making it valuable to investigate the treatment effects on different severity groups (13). Therefore, we designed this randomized trial to compare the treatment effect and safety of these two waveforms of EA stimulation for individuals with moderate or severe BP, categorized by their ENoG value of at least 20% or below 20% (15). This pilot study will assess the feasibility and safety of the treatment protocol, and has the potential to provide preliminary basis for subsequent research.

## Study objectives

2

This study is a protocol for a pilot randomized trial aimed at comparing the treatment effect and safety of EA with two different waveforms, the low frequency continuous waveform and the intermittent waveform, for different severity groups of BP.

## Materials and methods

3

The study protocol follows the Standard Protocol Items: Recommendations for Interventional Trials statement (33), and the trial will be in accordance with the Declaration of Helsinki and follow the Consolidated Standards of Reporting Trials (34) and the Revised Standards for Reporting Interventions in Clinical Trials of Acupuncture (35) guidelines. The trial was registered in ClinicalTrials.gov (ID: NCT06063954).

### Trial design and setting

3.1

This trial will be conducted at the Third Affiliated Hospital of Zhejiang Chinese Medical University, the First Affiliated Hospital of Zhejiang Chinese Medical University, and Hangzhou First People’s Hospital. The trial was approved and regularly reviewed by the research ethics committees of all three hospitals. The trial began in November 2023 and is expected to end in December 2025. Recruitment strategies included print posters displayed in outpatient departments and online posters on the WeChat social media platform. The intervention included a 4-week EA session, with different waveforms in each group. The trial procedure is shown in Figure 1, and schedule for allocation, treatment, and measurement is shown in Figure 2.

**Figure 1 fig1:**
[figure not shown]
Trial procedure. LFCW, Low frequency continuous waveform; IW, Intermittent waveform.

**Figure 2 fig2:**
[figure not shown]
Schedule of allocation, treatment, and measurement. LFCW, Low frequency continuous waveform; IW, Intermittent waveform.

### Participants

3.2

Potential eligible participants presenting with facial palsy will be recruited from the outpatient units of the acupuncture and moxibustion departments. Each eligible participant will receive a comprehensive explanation of the trial protocol before signing the informed consent. Eligible and consenting participants at each severity level will be randomly allocated to receive a 4-week EA treatment with the low frequency continuous wave pattern or the intermittent wave pattern in a 1:1 ratio.

Participants meeting the following criteria will be included: (1) Diagnosed as BP by neurology clinician; (2) Facial Nerve Grading System 2.0 (FNGS 2.0) is at least 15 on day 21 after the onset of BP; (3) Age between 18 and 65 years old; (4) Received prednisolone within 72 h after the initial symptoms of BP, the dose used was 60 mg per day for 5 days and then tapered by 10 mg per day; and (5) Signed informed consent.

Participants with any of the following conditions will be excluded: (1) Facial palsy caused by other diseases; (2) Diagnosed as Ramsey-Hunt syndrome; (3) Presenting bilateral facial palsy; (4) History of previous facial palsy; (5) Presenting with facial spasm, facial synkinesis, or contracture on day 21 after the onset of BP; (6) History of surgery on face; (7) Combined with uncontrolled diabetes mellitus, uncontrolled hypertension, serious conditions involving the heart, liver, or kidney, cognitive impairment, aphasia, or mental disorders; (8) Wearing a pacemaker; and (9) Pregnant or lactating patients.

The basic information and clinical data of each participants will be recorded using a case report form. And at each research center, an independent researcher will enter the data into an electronic data capture system (DAP Software Co., Ltd., China) in a timely manner.

### Randomization and allocation concealment

3.3

In total, 120 participants are planned to be enrolled from three clinical centers. Based on the patient volume and available resources at each center, we plan to recruit 70 participants from the First Affiliated Hospital of Zhejiang Chinese Medical University, 30 participants from the Third Affiliated Hospital of Zhejiang Chinese Medical University, and 20 participants from Hangzhou First People’s Hospital. For both severity levels, participants in all three clinical centers will be randomly assigned in a 1:1 ratio to the low frequency continuous wave group or the intermittent wave group using the same central computer system (DAP Software Co., Ltd., China) by an independent researcher at each clinical center. Allocation to treatment groups will be under the control of this system automatically, and therefore, will not be influenced by either researchers or participants.

### Blinding

3.4

In each clinical center, EA treatment will be provided by two acupuncturists, one for needle insertion and manipulation and the other for operation of the EA device. Acupuncturists who operate EA devices will not be blinded to the treatment allocation because the two treatment groups will receive EA treatment with different waveforms, and the EA device can only be operated manually. Acupuncturists who perform needle insertion and manipulation, participants, outcome assessors, and researchers for data management will be blinded to treatment assignment.

### Intervention

3.5

The two treatment groups will use the same acupoint prescription and needling method. Based on both traditional Chinese medicine literature and clinical experience, acupoint prescription will adhere to the principle of choosing both local and distal acupoints: BL2, GB1, GB14, ST2, ST4, ST6, ST7, SI18, SJ17, EX-HN5, EX-HN16, on the affected side, and LI4, bilaterally, as shown in Table 1 and Figure 3. Participants will be in a supine position, and after the skin sterilization, sterile and disposable acupuncture needles with 0.25 mm in diameter and 40 mm in length (Hwato Brand, Suzhou Medical Instrument, China) will be inserted into the prescript acupoints at a depth of 5 mm–30 mm and manually manipulated to elicit de-qi sensation. After needle insertion and manipulation, an SDZ-IIB EA device (Hwato Brand, Suzhou Medical Instrument, China) will be used to generate electrical stimulation, with a pair of electrodes connected to BL2 and GB1, and the other pair of electrodes connected to ST4 and ST6. In the low frequency continuous waveform group, EA with the 2 Hz continuous waveform will be used for 20 min, and in the Intermittent waveform group, EA with the 40 Hz intermittent waveform will be used for 20 min, the choose of 40 Hz for intermittent waveform stimulation was based on clinical experience and previous study (32). After the EA stimulation is completed, all needles will be removed to end the single treatment session. Besides EA treatment, no other treatment will be used for participants during the treatment period. Based on previous study on acupuncture therapy for BP (36), we set the treatment period to 4 weeks, during which participants will receive treatment three times a week, totaling 12 sessions.

**Table 1 tab1:** Locations of acupuncture points.

Acupoint	Location
BL2 Cuanzhu	In the depression at the medial end of the eyebrow.
GB1 Tongziliao	In the depression at 0.5 cun lateral to the outer canthus of the eye.
GB14 Yangbai	At 1 cun superior to the eyebrow, directly superior to the center of the pupil.
ST2 Sibai	In the infraorbital foramen.
ST4 Dicang	At 0.4 cun lateral to the angle of the mouth.
ST6 Jiache	At one fingerbreadth anterosuperior to the angle of the mandible.
ST7 Xiaguan	In the depression between the midpoint of the inferior border of the zygomatic arch and the mandibular notch.
SI18 Quanliao	At inferior border of the zygomatic bone, in the depression directly inferior to the outer canthus of the eye.
SJ17 Yifeng	In the depression anterior to the inferior end of the mastoid process.
EX-HN5 Taiyang	In the depression at one fingerbreadth posterior to the midpoint between the lateral end of the eyebrow and the outer canthus.
EX-HN16 Qianzheng	At 0.5–1 cun anterior to the auricular lobe.
LI4 Hegu	On the radial side of the midpoint of the second metacarpal bone.

**Figure 3 fig3:**
[figure not shown]
Illustration of the locations of selected acupoints.

### Outcome measurement

3.6

#### Primary outcome

3.6.1

*Change from baseline score of the Facial Nerve Grading System 2.0 at week 4.* The Facial Nerve Grading System 2.0 (FNGS 2.0) is an update version of the original House-Brackmann (H-B) scale (37). A study have shown that the inter-rater consistency when using the H-B scale is significantly influenced by the experience level of the assessors. In contrast, the FNGS 2.0 demonstrated better repeatability and consistency, independent of the assessor’s experience, indicating improved accuracy (38). Therefore, this pilot trial, we will use the FNGS 2.0 instead of the original H-B scale. In the FNGS 2.0, function of four facial regions including brow, eye, nasolabial fold, and oral commissure, and the global impression of secondary movement are separately assessed. Therefore, confusion can be addressed when different regions do not conform to a certain grade on the original H-B scale. Each area is assigned a score of 1–6, and the severity of secondary movement is assigned a score of 0–3, with higher score indicating poorer function. The final score is determined by combining the four regional and secondary movement scores. The primary outcome of this trial will be the change from baseline score of FNGS 2.0 at week 4.

#### Secondary outcome

3.6.2

*Change from baseline score of the Sunnybrook grading scale at week 4.* The Sunnybrook grading scale includes three subscales: the resting symmetry subscale, the symmetry of voluntary movement subscale, and the synkinesis subscale (39). Poorer function is indicated by a higher score in the resting symmetry subscale and the synkinesis subscale, and a lower score in the symmetry of voluntary movement subscale. The final score is calculated by subtracting the total resting symmetry score and total synkinesis score from the total voluntary movement score. In this trial, the change from baseline score of each subscale and the composite score will be calculated at week 4.

*Change from baseline value of the amplitude the CMAP of the affected side at week 4.* In the ENoG test, CMAP is the summated action potentials of the stimulated motor endplates following electrical stimulation to the facial nerve. In this trial, the ENoG test will be performed, and the change from baseline value of the amplitude of the CMAP of the affected side will be calculated at week 4 (40).

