### Statistical analysis

3.9

Statistical analysis will be performed using SAS software version 9.3 (SAS Institute Inc., United States). Numerical data with normal distribution will be presented as mean ± standard deviation, whereas non-normally distributed data will be shown as median and interquartile range. For categorical data, the frequency and percentage of each category will be presented. The Student’s *t* test or Mann–Whitney U test will be used for comparisons of numerical variables, and the chi-squared test or Fisher’s exact test will be used for comparisons of categorical variables. All statistical tests will be two-sided, with the significance level set at 0.05. Both intention-to-treat and per-protocol populations will be analyzed. Missing data will be substituted using the last observation carried forward method. After the primary statistical analysis, a power analysis will be conducted using G*Power software version 3.1.9.7 (Heinrich Heine University Düsseldorf, Germany) to evaluate the statistical power of the study given the sample sizes and the obtained effect sizes.

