The recovery time of the facial nerve function varies among patients with BP. Patients with quick recovery can restore complete function within 2–3 weeks since the onset of BP, while in severe cases, patients took 6 month to achieve full recovery or were left with varying degrees of sequelae (2). Prolonged facial asymmetry symptoms was reported to have more severe impact on daily living (52). Therefore, in this pilot trial, we plan to focus on patients with BP who do not experience a quick recovery. We will recruit patients with a score of at least 15 on FNGS 2.0 at day 21 after the onset of BP, with scores of 15–24 on FNGS 2.0 corresponding to Grade IV (moderately severe dysfunction) to VI (total paralysis) on the original H-B scale. We plan to investigate the efficacy and safety of the two waveforms of EA in two severity groups categorized by an ENoG value of at least 20% or below 20%, the results of this study have the potential to guide the clinical use of EA for different degrees of severity of BP.

Our study has several limitations. First, promoting the quick recovery of facial nerve function is important for all patients with BP, however, we will only include participants who presented with moderately severe to complete paralysis at day 21 after the onset of BP. Thus, the effects of EA in cases of mild severity will not be evaluated in this study. Second, in this study, we will not include a conventional acupuncture group or sham EA group. We expect to obtain the better EA waveform for treating BP in this trial, and we plan to verify its efficacy and safety by comparing it with conventional acupuncture or sham EA in future studies. Third, though in previous study of acupuncture therapy for BP, differences of symptom improvement among different treatment groups were observed after 4-week treatment (36), however, for patients with severe facial nerve impairment, the 4-week treatment period may be relative short. Moreover, we did not establish a post-treatment follow-up period to assess the long-term effects of the treatment. In future research, it is worth to explore the effect of longer treatment period, and also the long-term effect of EA for BP. Finally, although we plan to recruit patients from three hospitals to screen more potential participants, all of these hospitals are in the same city, which may lead to poor representativeness of the participants.

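### The CMAP secondary outcome is compared as unadjusted change in affected-side amplitude, although the trial needs both baseline amplitudes to form its severity levels; adjusting for them is a nearly free improvement (minor)

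*Protocol article*

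**What the plan says.** The Abstract lists as a secondary outcome "the change from baseline amplitude of the compound muscle action potential of the affected side in the ENoG tests". Section 3.6.2 agrees: "the change from baseline value of the amplitude of the CMAP of the affected side will be calculated at week 4". The data for it come from an ENoG test done as part of the study. No outcome based on the affected-to-healthy ratio is listed.

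The Introduction defines that ratio: "The ENoG value is calculated as the ratio of the CMAP amplitude on the impaired side to that on the normal side". The trial uses it to form its two strata; the Discussion speaks of "two severity groups categorized by an ENoG value of at least 20% or below 20" percent. Each stratum has 60 participants allocated 1:1 (section 3.8), which gives 30 per arm per level.

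For the comparison, section 3.9 says that the Student's t test or "Mann–Whitney U test will be used for comparisons of numerical variables", and that "All statistical tests will be two-sided, with the significance level set at 0.05". It names no covariate for numerical outcomes.

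**The concern.** A participant cannot be placed in a severity level without a healthy-side and an affected-side amplitude. Both are therefore available as baseline covariates, provided that the grouping ENoG is the baseline test. The stated comparison uses the affected-side baseline only by subtraction and does not use the healthy side.

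Subtracting baseline removes stable additive differences between patients. It does not remove a multiplicative one. If two patients gain the same 0.15 in ENoG value, and their healthy-side amplitudes are H and 2H, their raw changes are 0.15H and 0.30H. That spread has nothing to do with treatment and enters the error term of the t test. What is at stake is the precision of the trial's only instrumental outcome. A lesser point is that raw amplitude change cannot be read directly against the 20% threshold that defines severity.

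**Working it through.** **Inputs from the article.** 30 per arm within each level; two-sided 0.05; outcome and test as stated above. The article gives no SD, effect size, power target or test-retest error for CMAP, so there is no plan figure to reproduce.

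**Assumed inputs.** Gain in ENoG value: mean 0.15, SD 0.10, arm difference 0.075. Between-patient CV of healthy-side amplitude: c = 0.3 to 0.5.

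**Step 1: closed form, recovery on the ratio scale, no measurement error.** Scale the mean healthy amplitude H to 1 and take H and the gain g as independent. Raw change is H × g.

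- Unadjusted variance: 0.10² + c²(0.15² + 0.10²) = 0.0100 + 0.0325c².
- Variance after adjusting for both baseline amplitudes (H × 0.15 is removed): 0.10²(1 + c²).
- Standardised difference d = 0.075/SD; power from the noncentral t with 30 per arm.

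| c | Unadjusted variance | Adjusted variance | Variance ratio | d (unadjusted, adjusted) | Power (unadjusted, adjusted) |
|---|---|---|---|---|---|
| 0.3 | 0.0129 | 0.0109 | 1.19 | 0.66, 0.72 | 71%, 78% |
| 0.4 | 0.0152 | 0.0116 | 1.31 | 0.61, 0.70 | 64%, 76% |
| 0.5 | 0.0181 | 0.0125 | 1.45 | 0.56, 0.67 | 56%, 72% |

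This case favours adjustment, because measurement error is left out.

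**Step 2: simulation on the ratio scale with measurement error.** Side-specific noise CV 0.1–0.2 and shared session CV 0–0.2 are added. In the level below 20%, power runs over 38–64% for raw change and 41–70% for the two-baseline ANCOVA. With shared session CV 0.2, adjustment moves power by only -1 to +6 points.

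**Step 3: other recovery scales.**

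- Same gain added in amplitude units, unrelated to the patient's healthy amplitude: adjustment shows no gain beyond simulation error in any of 16 scenarios.
- Proportional growth of the affected-side amplitude (about 1.4-fold, 20% more in one arm): adjustment changes power by about -2 to +7 points. Almost all of this comes from the affected-side baseline; the healthy side adds about nothing.

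Over 48 settings covering the three recovery scales, the two-baseline ANCOVA differs from raw change by about -2 to +17 points.

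**Step 4: the ENoG ratio as the outcome.** Dividing by the healthy side removes patient scale but adds the healthy side's own error.

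- Under proportional growth, in the level of at least 20%, with session log-SD 0.2 and between-side error correlation 0.5, the sample size needed with raw change relative to ratio change is 1.00, 1.08, 1.29 and 1.67 for c = 0, 0.2, 0.4 and 0.6.
- Over all settings of that model it runs from 0.62 to 2.39. Below 1, the ratio is the noisier measure.
- With gain in amplitude units, the baseline-adjusted ratio has lower power than raw change in 11 of 16 scenarios. The largest loss is 30 points (78% to 48%).
- Over the 48 settings of step 3, the ratio ranges from about -30 to +34 points against raw change.

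**The case against.** The strongest reply is that nothing here is an error. The Abstract and section 3.6.2 agree, section 3.6.2 cites a source for the outcome, and affected-side amplitude measures the treated side directly. A stratifying variable and an outcome need not share a scale. The article is also condensed, and a separate analysis plan may name covariates. All of this stands as far as the choice of outcome goes, and it is why the amplitude should remain the outcome. It does not remove the point about the analysis, because section 3.9 does state a method for numerical variables, and that method is unadjusted.

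A second reply also stands: a benefit from adjustment depends on how recovery scales, and the article does not say. With recovery in plain amplitude units, adjustment gains nothing. A reader might infer that the planned form loses power in general. The documents do not support that, since they give neither a recovery scale nor variances.

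A reader might also infer that adjustment takes out session-to-session noise. A baseline covariate cannot remove noise arising at week 4. The ratio cancels only the error shared by both sides; with equal errors and no spread in patient scale, it helps only if the between-side correlation exceeds 0.5, and no such figure is given. Nor does the article say that healthy-side data are discarded. It merely does not use them in this outcome.

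**Conclusion.** The point holds as a minor one. Unadjusted change in raw affected-side amplitude can lose precision if recovery scales with the patient's own amplitude, and the covariates that could recover some of it are already needed for the grouping. The range of about -2 to +17 power points rests wholly on assumed variances, gains and recovery scales; its true place in that range is unknown. Steps 1 to 3 show little downside and, on some scales, a material gain.

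A reader might take this as bias between arms. It is not: allocation is randomised within severity level, so only imprecision is possible, in one of two secondary outcomes of a pilot. A reader might also conclude that the ENoG ratio should replace the amplitude. Step 4 shows that the ratio can be much more or much less precise, so it belongs beside the amplitude.

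**What to change.** In section 3.9, state that week-4 affected-side CMAP amplitude will be compared between arms by ANCOVA with baseline affected-side amplitude, baseline healthy-side amplitude and severity level as covariates. For analyses within one severity level, use the two baseline amplitudes only.

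Add one supportive row: week-4 ENoG value adjusted for baseline ENoG value, labelled as an aid to reading results on the scale that defines severity. This row needs the healthy side recorded at week 4, which performing the ENoG test implies but the article does not state; say so in section 3.6.2. Report the observed variability of both measures, so that the follow-on trial can choose between them on data.

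Cost: two degrees of freedom within a level (58 to 56 with 60 participants) or three when pooled (118 to 115 with 120), one model statement and one table row. The ANCOVA needs no new measurement.
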